## Discussion

3

This protocol aims to evaluate a digital speech therapy application for post-stroke dysarthria in a randomized clinical trial. This will establish the efficacy and feasibility of the intervention and contribute vital data to inform future trials. The scarcity of rigorous research on post-stroke dysarthria treatment means that these findings will be significant for researchers and clinicians in this field (18, 50).

Previous research has demonstrated the efficacy of behavioral speech treatment in patients with chronic post-stroke dysarthria. For instance, previous study showed a significant improvement in patients with post-stroke dysarthria after 16 sessions over 4 weeks (51). Similarly, another study reported positive outcomes from 60-min sessions administered four times a week for 1 month in patients with at least 6 months of post-stroke dysarthria (52). However, these studies may not fully address error patterns and stroke lesion characteristics across stroke recovery phases (53–55). They recognized the importance of early intervention, which has been shown to significantly enhance outcomes (34, 56, 57). Our protocol aims to fill this research gap by stratifying patients into acute to subacute, and chronic phases. This approach offers a comprehensive view of the effect of treatment on the stroke recovery spectrum.

Our study proposes digital speech therapy designed to address the limitations of traditional in-clinic or in-hospital treatments for post-stroke dysarthria. Considering the diverse error patterns in participants with post-stroke dysarthria, our system emphasizes the delivery of personalized therapies through speech assessment. We aim to enhance treatment efficacy and improve patient adherence using a patient’s smartphone application.

Maintaining long-term commitment to post-stroke treatment can be challenging (58, 59). Patients may exercise less frequently than suggested (60), struggle to achieve daily treatment goals (61), or discontinue therapy entirely (59). Digital solutions offered for comfort in patients’ homes are expected to encourage more intensive speech treatment (6) and better adherence. Digital speech therapy applications enable easier access to speech therapy, increase engagement, and may reduce costs (62, 63). However, this study has several limitations. First, the limited sample size might limit the applicability of our results. Second, our digital speech therapy application is designed exclusively for Koreans and targeted at native Korean speakers. This language limitation could limit the generalizability to non-Korean populations. Third, the lack of direct supervision by clinicians or SLPs in digital speech therapy interventions could affect patient motivation and result in higher dropout rates (59, 64). Finally, a significant challenge arises from the high proportion of older participants, which is typical in stroke patient demographics (65). Despite considering the design of our application for the elderly population, these participants may experience lower usability and adherence to digital treatment because of their unfamiliarity with digital technology.

Despite these limitations, this study has several strengths. First, it aims to provide new evidence for the use of digital speech therapy in the treatment of post-stroke dysarthria. This could increase the adoption of digital treatment in the field. Second, the study is designed to investigate whether a digital speech therapy application is effective and feasible for stroke participants, regardless of their severity and recovery stage.

In conclusion, this trial explores the efficacy and feasibility of digital speech therapy applications in treating post-stroke dysarthria. Our study aims to provide significant insights that will aid future research by refining effect size estimates and enhancing power analysis. By addressing the complexities of post-stroke speech therapy through a digital application, we expect to enhance treatment strategies. Through our trial, we expect to be able to provide evidence of digital therapeutics for the treatment of post-stroke dysarthria.

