## Introduction

1

Stroke is a leading cause of mortality and long-term disability (1). Stroke can elicit a range of neurological deficits or handicaps, including speech and language problems. Dysarthria is a neurologic motor speech disorder caused by disruptions in the cranial nerve and muscular control of the speech mechanism. It is estimated that approximately 22–60% of stroke patients experience dysarthria within the first week following a stroke (2–4). Approximately 35% of patients continue to exhibit dysarthria even after 6 months (5). Moreover, post-stroke dysarthria significantly impairs speech intelligibility and articulation movements (2). This impairment leads to substantial communication difficulties, emotional distress, social isolation, and poor quality of life (6, 7).

Interventions for dysarthria involve a range of strategies, such as neurorehabilitation, behavioral exercises, and social support (2). Behavioral speech exercises strengthen the breathing and oral muscles to improve speech control. Strategies such as slowing down speech or controlling pitch are also used to enhance speech intelligibility. The treatment plan should be personalized based on the patient’s prior communication ability, recovery stage, and needs (8).

Despite the critical need for effective treatment of dysarthria, traditional therapies are often limited by their monotonous repeated nature. Consequently, these challenges can result in reduced treatment adherence (9). Moreover, the significant time and effort required by physicians and speech-language pathologists (SLPs), often restricts patient access to necessary therapeutic resources (10). Studies have indicated that only approximately one-third of patients receive adequate speech therapy, with substantial variations in therapy frequency (11). Given these limitations, personalized dysarthria treatment becomes necessary because of the diverse patterns of speech impairment in post-stroke dysarthria caused by different stroke lesions (12). These observations highlight the urgent need for alternative approaches, such as personalized digital speech therapy.

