Compared with traditional in-clinic methods, these digital applications offer substantial benefits. These include the ability for patients to engage in various speech exercises from home. They improve treatment precision, enhance economic efficiency, ensure patient safety, maintain continuity of care, and support self-management (13, 14). This approach reduces the need for clinic visits and related expenses (15, 16). Furthermore, digital therapy is especially beneficial during the COVID-19 pandemic or endemic as it allows patients to continue their therapy without interruption (17).

Additionally, there is a noticeable lack of high-quality, comprehensive research on the treatment of post-stroke dysarthria. Many existing randomized controlled trials on post-stroke dysarthria have been on a small scale, limiting their ability to provide conclusive evidence regarding the effectiveness of various treatments (18). This significant research gap highlights the importance of our study, which aims to investigate both the efficacy and feasibility of a personalized digital speech therapy application for participants with post-stroke dysarthria.

This study aims to investigate the efficacy and feasibility of a digital speech therapy application for patients with post-stroke dysarthria. Ultimately, our trial seeks to establish our digital speech therapy application as a comprehensive solution. Our application strives to enhance the accessibility and practicality of post-stroke dysarthria. It provides personalized treatments tailored to each patient’s unique needs, thereby overcoming the limitations of traditional rehabilitation methods (12). We hypothesize that our digital speech therapy application would be non-inferior to conventional speech therapies in enhancing patient speech intelligibility and function for post-stroke dysarthria. Additionally, we anticipate positive impacts of our digital speech therapy application on psychological well-being, such as reduced depression and improved quality of life in patients with post-stroke dysarthria. Furthermore, this trial will assess the feasibility of this innovative approach in a clinical setting. It will focus on critical aspects such as recruitment and retention rates, participant adherence, safety, and gathering user feedback.

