#### Control group

2.5.2

Participants allocated to the control group will undergo conventional therapy for post-stroke dysarthria over 4 weeks. In the absence of a standard protocol for post-stroke dysarthria treatment in South Korea, we have developed a conventional speech therapy workbook. This workbook integrates various clinically validated behavioral therapy techniques (2, 34). Its content is aligned with the intervention group’s digital speech therapy application to ensure consistency in treatment approaches. Participants will engage in the workbook for 60 min daily, 5 days a week, for 4 weeks to match the intervention group’s treatment dose and frequency. The workbook ensures treatment consistency across the multiple centers involved in this clinical trial. Before starting therapy, the researchers will guide the participants using the conventional therapy workbook.

In line with the intervention group, occasional guidance or support from family members will be allowed. This approach ensures that both groups have access to similar levels of support. By doing so, we promote equality in the treatment conditions across the groups. During regular follow-ups, researchers will monitor the extent and nature of any assistance family members provide. This monitoring will help ensure that the level of support remains balanced and appropriate for both groups.

Researchers will conduct daily follow ups to ensure adherence to conventional therapy workbook. During these interactions, researchers will discuss the participants’ progress, address challenges, and provide support and encouragement to maintain consistent participation in therapy. This approach ensures that the control group receives the same level of attention and support as the intervention group, thereby maintaining trial integrity. After the clinical trial, participants in the control group will also have access to the digital speech therapy application.

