### Analysis

2.7

The primary objective of this trial is to investigate the non-inferiority of the intervention group compared to the control group in terms of changes in speech intelligibility from baseline to post-treatment. The hypothesis is as follows:

$$H_{0}:\mu_{t}-\mu_{c}<\delta \;vs\;H_{1}:\mu_{t}-\mu_{c}\geq \delta$$

Where *μt* is the mean change in speech intelligibility score in the intervention group using the digital speech therapy application, and *μc* is the mean change in the control group receiving conventional speech therapy. It is assumed that there is no difference between the two groups, and this study seeks to establish the non-inferiority of the groups. The non-inferiority margin *δ* is set at 19 points, based on the assumption that a difference of 1 to 19 points on the speech intelligibility scale is clinically non-inferior (45).

The sample size required for the non-inferiority trial was determined using a statistical formula (46). This involved setting the significance level (alpha) to 0.025 for a one-sided test and targeting a power of 80% (*β* = 0.2) (47) with a standard deviation of 24.9 (48). This calculation revealed that 28 participants are required for each group. A total of 56 participants are required for the trial. To account for a possible dropout rate of 30%, we aim to recruit a total of 76 participants, with 38 participants in each group.

$$n=\frac{2{\left(z_{\alpha }+z_{\beta }\right)}^{2}\sigma^{2}}{{\left(\mu_{t}-\mu_{c}-\delta \right)}^{2}}\approx 28$$

Analyses will be performed using SPSS software (version 27; IBM Corp., Armonk, New York). Descriptive statistics will summarize the demographic data and outcome measures. For interval estimates, 95% confidence intervals will be provided. An intention-to-treat (ITT) analysis will include all randomized participants. Additionally, we will conduct a per-protocol (PP) analysis which includes only participants who fully adhered to the intended protocol.

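### Non-inferiority to the team's own workbook cannot by itself establish the app's efficacy, as the Discussion says it will

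*Protocol article*

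**What the plan says.** The first paragraph of the Discussion says of the trial: "This will establish the efficacy and feasibility of the intervention and contribute vital data to inform future trials".

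The sections on trial design and randomization describe two treated arms allocated 1:1, with no untreated or sham arm. The primary outcome is change in speech intelligibility over 4 weeks. Both strata lie within 6 months of onset: up to 1 month, and 1 to 6 months.

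On the comparator, the Control group section says: "In the absence of a standard protocol for post-stroke dysarthria treatment in South Korea, we have developed a conventional speech therapy workbook". It calls the component techniques clinically validated, citing two sources, and says that content and dose match the app. Researchers give initial guidance and follow up daily. No delivery by a therapist is described.

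The Introduction words the hypothesis more broadly: "We hypothesize that our digital speech therapy application would be non-inferior to conventional speech therapies in enhancing patient speech intelligibility and function". The Analysis section sets a 19-point margin on "the assumption that a difference of 1 to 19 points on the speech intelligibility scale is clinically non-inferior".

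The limitations in the Discussion cover sample size, language, lack of direct supervision and older participants. They mention neither the lack of an untreated arm nor spontaneous recovery.

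**The concern.** A non-inferiority result shows that the new treatment is not worse than the control by more than the margin. It shows benefit over no treatment only when the control's own benefit is known, in the same population and period, to exceed that margin. The article gives no effect of this workbook over no treatment, for any population. The margin is justified by what loss is acceptable, not by what the control is known to deliver.

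If the workbook adds little, an app that also adds little can pass the test, and under the Discussion's wording would be reported as efficacious. A result against this workbook also speaks to this workbook only, whereas the hypothesis refers to conventional speech therapies in general.

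**Working it through.** **Inputs** (Analysis section): margin 19 points, SD 24.9, one-sided alpha 0.025, power 80%, true difference 0, 28 per group needed, 38 per group recruited. I take 24.9 as the SD of the change score, and non-inferiority as a lower 95% limit for app minus workbook above −19.

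**1. The plan's own figure.** n = 2 × (1.960 + 0.842)² × 24.9² / 19² = 26.96, so 27 per group by the normal approximation. The t-based calculation gives 28 (power 80.1%). The stated 28 is reproduced.

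**2. Precision at 28 per group.** SE = 24.9 × √(2/28) = 6.65, and the half-width of the 95% interval is 1.96 × 6.65 = 13.04. An observed deficit of up to 19 − 13.04 = 5.96 points therefore still passes. At 38 per group SE = 5.71, the half-width is 11.20 and the passing deficit is up to 7.80 points.

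**3. Chance that an app with no specific effect passes.** Let c be the workbook's true gain over no treatment. The true difference is then −c, and

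P(declare non-inferior) = Φ((19 − c)/SE − 1.96).

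| Assumed c (points) | 28 per group | 38 per group |
|---|---|---|
| 0 | 81.5% | 91.4% |
| 5 | 55.7% | 68.8% |
| 10 | 27.2% | 35.0% |
| 15 | 8.7% | 10.4% |
| 19 | 2.5% | 2.5% |

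For example, at c = 5 with 28 per group: (19 − 5)/6.65 − 1.96 = 0.14, and Φ(0.14) ≈ 0.557. The error is held to 2.5% only when the workbook's gain is at least 19 points. The document does not give c.

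**4. What a superiority reading would need.** The lower 95% limit exceeds 0 only if the app's observed advantage exceeds 13.04 points (28 per group) or 11.20 points (38 per group). If the true difference is 0, as the sample size assumes, this happens 2.5% of the time. For a true advantage a, power is Φ(a/SE − 1.96). At 28 per group this is 8.7%, 27.2%, 55.7% and 81.5% for a = 4, 9, 14 and 19, the table's figures with a = 19 − c.

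**5. Evidence offered for the control.** The Discussion describes two positive studies of behavioral treatment under chronic dysarthria. One is in patients with at least 6 months of dysarthria, outside this trial's strata apart from the boundary. No time since onset is given for the other. The Introduction itself says existing trials are too small to be conclusive about treatments. None of this supplies a value of c for the workbook.

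**The case against.** The strongest reply is that a single sentence is being held against a document that is elsewhere careful. The abstract's conclusion speaks of possible foundational evidence, the closing paragraph says the trial explores efficacy, and the Analysis section states only that "this study seeks to establish the non-inferiority of the groups". No test or decision rule depends on the Discussion sentence. This stands as context and makes the correction easy, but the sentence still asserts something the design cannot deliver.

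The 81% is also no defect in itself. It is the designed power when the arms are equal, and any active-controlled trial without an untreated arm shares the property. That is right. But the test cannot tell equal and useful from equal and useless. Because app and workbook share content and dose, an effective workbook beside an inert app is less plausible, so the middle rows deserve less weight. Both adding little is not excluded in the same way.

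Three stronger readings are tempting and are not supported:

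- A reader might infer that the protocol claims parity with conventional therapy. It does not: non-inferiority is hypothesised and sought, not asserted as a result.
- A reader might infer that the article's figures prove substantial natural recovery, from 22–60% with dysarthria in the first week to this: "Approximately 35% of patients continue to exhibit dysarthria even after 6 months". But 35% lies inside 22–60%, the denominators are unclear, and neither figure describes a 4-week window. Spontaneous recovery remains a possibility to acknowledge, not a documented quantity.
- A reader might call the workbook unproven outright. The article cites sources for its techniques and for the value of early intervention. What is missing is an effect for the workbook as a package in this population.

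Finally, adding a superiority test to a trial sized for no difference can look like design preference. It is offered only as the route by which an efficacy claim could be earned.

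**Conclusion.** The Discussion's efficacy statement is wrong as written and should be corrected. The design supports a conclusion about the app relative to this workbook, within 19 points. It supports efficacy only if the workbook's gain over no treatment is known to exceed 19 points in patients within 6 months of stroke, and the article gives no such figure.

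With 28 per arm, an app with no specific effect passes with a probability between about 81% (workbook gain 0) and 2.5% (gain 19). That range rests on the plan's SD and margin and on assumed values of the workbook's gain. The conclusion does not depend on any particular value, nor on the prevalence figures. The non-inferiority test remains a usable comparison with the workbook; the fault lies in what the Discussion says it will show.

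**What to change.** 1. In the Discussion, replace the efficacy statement with a conclusion limited to the app being no worse than the self-directed workbook by more than 19 points. In the Introduction, word the hypothesis as non-inferiority to the workbook rather than to conventional speech therapies in general.
2. Pre-specify a fixed sequence. If non-inferiority is met, read superiority over the workbook (lower 95% limit above 0) from the same interval at one-sided 0.025, and let only that support an efficacy claim. This assumes the workbook is not worse than no treatment. State that power for this step is low because the trial is sized for a true difference of zero.
3. Add the lack of an untreated arm and possible spontaneous recovery to the limitations. State that within-group change, including the within-group regressions by stroke phase in the Analysis section, will not be read as a treatment effect.

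The cost is wording and one further reading of an interval already planned. The fixed sequence spends no alpha, and no patients or procedures are added. The downside is a more modest claim.

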## Ethics statement

The studies involving humans were approved by the EWHA Womans University Seoul Hospital Institutional Review Board (EUSMC-2021-12-011) and the National Rehabilitation Center Institutional Review Board (NRC-2023-01-007). The studies were conducted in accordance with the local legislation and institutional requirements. The participants provided their written informed consent to participate in this study. Written informed consent was obtained from the individuals for the publication of any potentially identifiable images or data included in this article.
